### Data monitoring body

Our monitoring staff will be responsible for reviewing the various records of the study and confirming the enrollment status; research plan compliance; completeness, accuracy, and consistency of the data; and compliance with ethical guidelines. The monitoring staff will confirm the contents of the case report forms and ensure research integrity. In addition, the monitoring staff will oversee and manage the condition of each device. The monitoring staff will report any deviations from the protocol, its various procedures, and applicable regulatory requirements to the principal investigator and confirm that appropriate measures are taken and recorded in order to ensure that any identified deviations do not recur. The principal investigator agrees to cooperate with the monitoring staff to ensure that all issues discovered during such monitoring are handled and recorded.

### Sample size calculation

The target sample size is based on previous reports (Table 3). In this study, patients will be divided into three groups based on their neurological severity at enrollment, and the functional outcome at 3 months after stroke onset will be determined for each group. A good functional outcome will be defined as mRS scores of 0–1, 0–2, and 0–3 for the mild (NIHSS score at enrolment, 5–9), moderate (NIHSS score at enrolment, 10–14), and severe (NIHSS score at enrollment, 15–20) groups, respectively. We hypothesize that the rates of good functional outcome are 35 and 50% in the control and RIC groups, respectively; accordingly, with 80% power at the 5% significant level, a sample size of 334 patients is necessary. Furthermore, to account for an expected drop-out rate of 10% (e.g., withdrawal of consent, lost to follow-up), we plan to enroll a total of 400 patients.

**Table 3 T3:** Previous reports on the relationship between the NIHSS on admission and modified Rankin Scale at discharge or 3-months after stroke onset.

**References**	**Year**	**No. patients**	**NIHSS on admission, median (IQR)**	**Severity**	**Therapy**	**mRS (%)**						
						**0**	**1**	**2**	**3**	**0–1**	**0–2**	**0–3**
Thomalla et al. (1)	2018	249	6 (4–9)	Mild	Placebo	15	27	23	17	42	70	87
Lees et al. (14)	2006	847	14.5	Moderate	Placebo	11	20	12	13	31	43	58
Shuaib et al. (15)	2007	1,631	13.8	Moderate	Placebo	10	18	15	15	29	43	58
Shuaib et al. (16)	2011	249	10 (2–20)	Moderate	Control	0	32	12	17	32	44	59
Ginsberg et al. (17)	2013	419	11 (8–17)	Moderate	Placebo	15	23	18	15	38	56	71
Hess et al. (18)	2017	61	13 (8–20)	Moderate	Placebo					12	36	
Saver et al. (19)	2015	843	11.2 (9.8)	Moderate	Placebo	18	16	18	13	35	53	66
Elkins et al. (20)	2019	78	12 (2–29)	Moderate	Placebo	5	15	15	19	20	35	54
Kimura et al. (21)	2003	1,342	0–4							75		94
		1,020	5–9	Mild						41		75
		602	10–14	Moderate						20		46
		521	15–20	Severe						8		23
Goyal et al. (2)	2016	100	<10	Mild	Medical	14	13	28	15	28	55	71
		140	11–15	Moderate	Medical	7	11	16	20	17	34	54
		236	16–20	Severe	Medical	3	4	12	17	8	20	30
Hill et al. (22)	2020	556	17 (13–21)	Severe	Placebo	19	22	19	11	41	59	70
Nogueira et al. (23)	2018	99	17 (14–21)	Severe	Medical	4	5	4	16	9	13	29
Albers et al. (24)	2018	90	16 (12–21)	Severe	Medical	8	4	4	16	12	16	32

IQR, interquartile range; mRS, modified Rankin Scale; NIHSS, National Institutes of Health Stroke Scale; rt-PA, recombinant tissue-type plasminogen activator.

### Statistical analysis

The target populations for analysis will be defined as follows. The full analysis set (FAS) will comprise all randomized participants, with the exclusion of those who never received any protocol treatment, those who underwent at least one protocol treatment but whose post-protocol data are not available, and those who did not meet the eligibility criteria. The intention-to-treat population will comprise all subjects who underwent randomization. The per-protocol set will comprise those in the full analysis set, with the exclusion of subjects with remote ischemia and poor conditioning compliance (<80%). The population for the safety analysis will comprise all subjects who received at least one protocol treatment.

### Statistical analysis of the primary outcome

The primary outcome (a good outcome based on the mRS score at 90 days after stroke onset) will be reported as the percentage. Percentage differences between the RIC and control groups will be evaluated using the Chi-square test. Additionally, multiple regression analysis will be performed. For the multiple regression analysis, corresponding odds ratios and 95% confidence intervals will be calculated, and a *P*-value <0.05 will be considered to be statistically significant.

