### Randomization

The patients will be divided according to their National Institutes of Health Stroke Scale (NIHSS) score at enrollment: 5–9, mild; 10–14, moderate; 15–20, severe. Randomization will be performed using a predefined table generated by a computer program, and the results of the assignment will be immediately sent to the physician in charge *via* a computer. To eliminate bias, the assigned study groups will not be disclosed to the evaluating physician during evaluation of mRS at 90 days post stroke. All other staff will have access to the study arm and test results of the participants.

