### Primary outcome

The primary outcome will be a good functional outcome at 3 months after stroke onset, with a target mRS score of 0–1, 0–2, and 0–3 in the mild, moderate, and severe groups, respectively. The mRS scores will be determined by face-to-face assessments or structured telephone interviews performed by various assessors, who will be blinded to the allocation results.

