### Statistical analysis of secondary outcomes

Percentage differences between the RIC and control groups in terms of the incidence of MACE, aspiration pneumonia, frequency of adverse RIC-related events, and all-cause mortality within 90 days will be evaluated using the Chi-square test. The change in NIHSS score from the time of enrollment to 1 week later will be evaluated in a two-sided analysis of variance, with α = 0.05 and power = 0.80. Additionally, with stratified analysis, we will compare the differences in the achievement rate (percentage) of the primary outcome in the RIC and control groups according to the severity of the disease at the time of enrollment (mild, moderate, and severe groups), age (dichotomized by the median of all enrolled patients), sex, presence of occlusion or severe stenosis of the main cerebral artery, treatment with rt-PA and/or EVT, and presence of diabetes mellitus.

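### The primary outcome is tested by a Chi-square that ignores severity, a regression of the same outcome is added with its own significance criterion, and the plan does not say which decides

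*Protocol article*

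**What the plan says.** The section on analysis of the primary outcome gives two analyses of the same binary endpoint. The first: "Percentage differences between the RIC and control groups will be evaluated using the Chi-square test". The second: "Additionally, multiple regression analysis will be performed", for which "corresponding odds ratios and 95% confidence intervals will be calculated, and a *P*-value <0.05 will be considered to be statistically significant". The Chi-square sentence carries no threshold of its own, and no covariates are listed for the regression. Neither analysis is called primary, confirmatory or supportive.

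The endpoint depends on baseline severity: success is set "with a target mRS score of 0–1, 0–2, and 0–3 in the mild, moderate, and severe groups, respectively". Under Randomization the article says "The patients will be divided according to their National Institutes of Health Stroke Scale (NIHSS) score at enrollment: 5–9, mild; 10–14, moderate; 15–20, severe". In the stated analysis, severity appears explicitly only under secondary outcomes, where the achievement rate is to be compared "according to the severity of the disease at the time of enrollment (mild, moderate, and severe groups", alongside age, sex and other factors.

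The sample size rests on a single pooled comparison: "We hypothesize that the rates of good functional outcome are 35 and 50% in the control and RIC groups, respectively", at 80% power and the 5% level, giving 334 patients, raised to 400 for drop-out.

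**The concern.** Severity group fixes what counts as success and is known for every patient at enrolment, yet the first-named test of the primary outcome leaves it out. Baseline NIHSS and age are also recorded at screening. An analysis that leaves out known prognostic information gives away power that would cost nothing to keep.

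The second issue is that the plan holds two analyses of one outcome and no rule for when they disagree. They report different quantities, a difference in percentages and an odds ratio. The trial is open-label, and apart from the day-90 mRS assessor all staff can know the allocation, so the choice of headline result should not remain open until the data are in.

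**Working it through.** **Reproducing the plan's figure.** Two proportions, 35% and 50%, two-sided 5%, 80% power, 1:1, unpooled variance:

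n per arm = (1.960 + 0.842)² × (0.35×0.65 + 0.50×0.50) / 0.15² = 7.849 × 0.4775 / 0.0225 = 166.6, so 167 per arm and 334 in total.

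This matches exactly (the pooled-variance version gives 340). The trial was therefore sized for an unadjusted comparison. With 10% drop-out, 400 × 0.9 = 360 evaluable patients, at which the closed-form power is 82.4%.

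**Assumptions taken from Table 3.**
- Severity mix: the 2003 report with NIHSS bands 5–9, 10–14 and 15–20 has 1,020, 602 and 521 patients, i.e. 48/28/24%.
- Control success, main scenario, 41/34/23%: mRS 0–1 at NIHSS 5–9 and mRS 0–3 at NIHSS 15–20 from that report; mRS 0–2 at NIHSS 11–15 from the 2016 medical-arm report. The pooled rate is 0.476×0.41 + 0.281×0.34 + 0.243×0.23 = 34.7%, close to the planned 35%.
- Control success, widely differing scenario, 28/34/70%: the first two from the 2016 report, 70% from the 2020 placebo group with median NIHSS 17.
- Effect: a common odds ratio of (0.50/0.50)/(0.35/0.65) = 1.857.

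**How much severity explains.** Between-group variance divided by total variance:
- 41/34/23%: 0.0052 / (0.347×0.653) = 0.0052/0.227 = 2.3%.
- 28/34/70%: pooled rate 39.9%; 0.0298 / (0.399×0.601) = 0.0298/0.240 = 12.4%.

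A rough approximation scales the 2.80 standard errors needed for 80% power by 1/√(1 − share explained). This gives 2.80/√0.977 = 2.83, power Φ(2.83 − 1.96) = 81%, a gain of about 1 point. For the second scenario, 2.80/√0.876 = 2.99, power Φ(1.03) = 85%, a gain of about 5 points.

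**Simulation at n = 360** (3,000 trials under the effect, 6,000 under the null; regression adjusted for severity only; all entries in %):

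| Control rates | Balanced by severity | Power: crude | Power: CMH | Power: logistic | Null error: crude | Null error: either test |
|---|---|---|---|---|---|---|
| 41/34/23 | yes | 79.9 | 80.5 | 80.7 | 4.6 | 5.0 |
| 41/34/23 | no | 79.8 | 80.8 | 80.9 | 4.9 | 5.6 |
| 28/34/70 | yes | 75.7 | 79.5 | 79.6 | 3.7 | 5.3 |
| 28/34/70 | no | 71.4 | 76.5 | 76.6 | 5.5 | 7.0 |

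Monte Carlo standard errors are about √(0.8×0.2/3000) = 0.7 points for power and √(0.05×0.95/6000) = 0.3 points for null error. The tests are compared on the same simulated trials.

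**Adding NIHSS and age.** The documents give no effect sizes for these. With assumed log-odds ratios of −0.20 to −0.25 per NIHSS point within severity group and −0.5 to −0.8 per SD of age, a separate simulation at 35% vs 50% gives 81.0–81.7% power for the crude test and 84.3–86.7% for the adjusted logistic model. Modest to moderate assumed effects at 41/34/23% give a gain of 2 to 4 points.

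**If either result counted.** When the regression also adjusts for one strong covariate (assumed log-odds ratio 1 per SD), an either-test rule rejects in 6.5–7.3% of null trials. The value for two independent tests, 1 − 0.95² = 9.75%, does not apply because the two tests are strongly correlated. Under the effect, the two verdicts differ in 0.2–10% of trials with severity-only adjustment across the scenarios run, and in 13–17% with the strong covariate.

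**The case against.** The best defence is that the order is implicit. The Chi-square comes first, the regression is introduced as an addition, and the 334 is an unadjusted two-proportion figure at the 5% level. That makes the Chi-square the likelier lead test. It does not settle the matter, because the only significance criterion in the primary-analysis section is attached to the regression.

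The sliding mRS cut is itself meant to allow for severity. At 41/34/23%, severity explains about 2% of outcome variance, against about 10% for a fixed mRS 0–1 cut in the NIHSS-banded report (41/20/8%). This stands, and it is why the loss from ignoring severity alone is small in that scenario.

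Four stronger readings are tempting, and the document does not support them:
- That the plan gives two chances to win at 5% each. No sentence says that significance on either analysis would establish efficacy; the 5 to 7% is conditional on a rule that the document does not contain.
- That the crude test is invalid. It is valid, and slightly conservative if allocation is balanced by severity.
- That the analysis departs from a stratified randomization. The article says that patients are divided by NIHSS but never states that randomization is stratified.
- That severity is absent from the plan. It is in the secondary comparison and may be among the regression's covariates. A full covariate list can properly sit in a document not shown here, so its absence is no fault.

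**Conclusion.** The point holds as a moderate one. What the article states is an unadjusted test for an endpoint defined by severity, plus a second analysis of the same endpoint with its own criterion, and no statement of which decides.

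The efficiency loss from ignoring severity is about 1 point of power at 41/34/23% and about 3 to 5 points if success rates differ strongly by severity. A few further points depend on assumed effects of NIHSS and age, so power as high as 84–87% should not be presented as a property of this trial. With the pooled 35% and 50% taken at face value, the crude test still reaches the planned 80% at 360 patients.

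The clearer defect is the unnamed decisive analysis: the two verdicts can conflict, and the article offers no way to resolve this.

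**What to change.** Name one confirmatory analysis of the primary outcome at two-sided 0.05: a logistic regression of good outcome on arm, adjusted for severity group, baseline NIHSS and age. A Cochran-Mantel-Haenszel test stratified by severity is an acceptable alternative. Report the odds ratio and the adjusted risk difference, each with a 95% confidence interval; the risk difference keeps the link to the planned 35% versus 50%. Label the crude Chi-square as supportive, and say that it cannot establish success on its own. Record the choice before outcomes are examined by arm.

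The cost is about two sentences. NIHSS and demographic data are already collected at screening (Table 2), and the sample size does not need to change.

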### Statistical analysis of secondary outcomes

Percentage differences between the RIC and control groups in terms of the incidence of MACE, aspiration pneumonia, frequency of adverse RIC-related events, and all-cause mortality within 90 days will be evaluated using the Chi-square test. The change in NIHSS score from the time of enrollment to 1 week later will be evaluated in a two-sided analysis of variance, with α = 0.05 and power = 0.80. Additionally, with stratified analysis, we will compare the differences in the achievement rate (percentage) of the primary outcome in the RIC and control groups according to the severity of the disease at the time of enrollment (mild, moderate, and severe groups), age (dichotomized by the median of all enrolled patients), sex, presence of occlusion or severe stenosis of the main cerebral artery, treatment with rt-PA and/or EVT, and presence of diabetes mellitus.

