### Intervention

For all patients, a manual blood pressure cuff will be placed around the lower leg or thigh of the unaffected side, and blood pressure will be measured while detecting the dorsalis pedis artery using an ultrasonic Doppler blood flow meter. The intervention (RIC) group will receive four cycles of 5 min of blood pressure cuff inflation, followed by 5 min of reperfusion. Cuff inflation in the RIC group will be set at 200 mmHg or 50 mmHg above the systolic blood pressure; however, if the patient cannot tolerate this, the cuff pressure may be reduced to 180 mmHg. This procedure will be performed once daily after enrollment, for a minimum of 3 days and a maximum of 7 days. In contrast, the control group will only undergo blood pressure measurements before and after the intervention period (the 40-min duration required for four cycles of RIC). Discomfort and pain will be assessed using a verbal rating scale ranging from 0 to 4 (0, no pain; 1, mild pain; 2, moderate pain; 3, severe pain; 4, very severe pain) (13).

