### Secondary outcomes

The secondary outcomes will be the proportion of patients with good functional outcome (assessed by the mRS) in each group at 3 months after stroke onset; change in NIHSS scores from before RIC to after RIC; incidence of major adverse cardiovascular events (MACE), aspiration pneumonia, and all-cause mortality within 90 days after stroke onset; frequency of adverse RIC-related events; and proportion of patients with an mRS score of 0–1.

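### The between-arm chi-square test of RIC-related adverse events does not fit its outcome: on the plain wording only the RIC arm can have such an event

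*Protocol article*

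**What the plan says.** The Secondary outcomes section of the protocol article lists "frequency of adverse RIC-related events" and does not define the term further. The section on the statistical analysis of secondary outcomes plans a two-arm test of it, RIC against control: "frequency of adverse RIC-related events, and all-cause mortality within 90 days will be evaluated using the Chi-square test".

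On treatment, the Intervention section says that "the control group will only undergo blood pressure measurements before and after the intervention period". It also says: "For all patients, a manual blood pressure cuff will be placed around the lower leg or thigh of the unaffected side". Both arms therefore have brief leg-cuff exposure for measurement, but only the RIC arm has the inflation cycles.

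On blinding, the Randomization section withholds the allocation from the physician who rates the 90-day mRS, and continues: "All other staff will have access to the study arm and test results of the participants".

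Table 2 schedules adverse-event confirmation and the pain questionnaire at every visit, from screening to day 90.

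**The concern.** Attribution to RIC is part of the outcome's name. A patient who never had RIC cannot, in the ordinary sense of the words, have an event related to it. Testing the difference between arms then sets the RIC-arm count against a zero that the wording fixes in advance.

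This can mislead in two ways. A significant result shows only that some events were attributed to RIC among patients who had RIC, which the count already shows. A non-significant result can be read as no excess harm, although harm was not compared. In addition, a local leg problem that staff put down to the stroke or to bed rest drops out of this item in the RIC arm, and a similar problem in a control never enters it.

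The other events tested in the same sentence are cardiovascular events, pneumonia and death. None of them captures local harm from the cuff, so for that class of harm the article names only the attributed outcome.

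**Working it through.** The article states no event rate, target difference or sample size for this outcome, so there is no figure of its own to reproduce.

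**Inputs.** There are 200 patients per arm (Abstract). Let x be the number of RIC patients with at least one RIC-related event. The control count is 0, from the plain wording of the outcome and the Intervention section.

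**1. Uncorrected chi-square.** For x/200 against 0/200:

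χ² = 400·(200x)² / [200·200·x·(400 − x)] = 400x / (400 − x)

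Only x remains in the formula, so the control arm adds no information beyond its size.

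- x = 3: 1200/397 = 3.02, P = 0.082
- x = 4: 1600/396 = 4.04, P = 0.044

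**2. Yates-corrected chi-square.**

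χ² = 400·(200x − 200)² / [200·200·x·(400 − x)] = 400(x − 1)² / [x(400 − x)]

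- x = 5: 6400/1975 = 3.24, P = 0.072
- x = 6: 10000/2364 = 4.23, P = 0.040

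**3. Fisher's exact test.** With all events in one arm, the two-sided P is 2·C(200, x)/C(400, x).

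- x = 5: P = 0.061
- x = 6: P = 0.030

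The thresholds are thus 4/200 (2%) uncorrected and 6/200 (3%) by Yates or Fisher. They stay at 4 and 6 with 180 or 167 patients per arm. With 4 to 8 events in all, the expected count per arm is x/2 = 2 to 4, below the usual minimum of 5 for a chi-square test, so the choice of variant matters here.

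**4. Chance of P < 0.05.** The documents give no rate of RIC-related events, so the rates below are assumptions. The chance is the binomial probability, with n = 200, of reaching the threshold.

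| Assumed rate in RIC arm | Uncorrected (at least 4) | Yates or Fisher (at least 6) |
|---|---|---|
| 1% | 14% | 2% |
| 2% | 57% | 21% |
| 3% | 85% | 56% |
| 5% | 99% | 94% |
| 10% | about 100% | about 100% |

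The outcome of the test follows from how often events are attributed to RIC in the RIC arm, and from nothing that happens in controls.

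**5. Data for a proper comparison.** Table 2 puts no arm restriction on adverse events or pain. No row of that table separates the arms, the RIC row included, so I read it as the schedule for all patients, except that RIC itself is given to one arm. On that reading, attribution-free data are already planned in both arms.

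**The case against.** The strongest reply is that the zero is inferred. The article does not define the outcome, and the label could stand for events of the kind that RIC may cause, such as leg pain or skin injury, whatever their cause. All patients have a leg cuff placed for measurement, so a control could have such an event, and planning a two-arm test fits that reading. Detailed event definitions are also commonly left to a full protocol. This stands as a limit: it cannot be said that controls are at zero under every definition. It does not rescue the text as it is, because on that reading the name is wrong and must change.

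Second, a reader might infer that the trial has no sound safety comparison. The documents do not support that. MACE, aspiration pneumonia and all-cause mortality are compared between arms without regard to attribution and can occur in either arm. The frequency of RIC-related events within the RIC arm is also informative in itself.

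Third, a reader might infer that unblinded staff are known to decide relatedness. The Randomization section makes this likely, since only the 90-day mRS rater is kept unaware of the arm, but the article does not say who judges causality.

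Fourth, any test near its threshold turns on one or two events, so sensitivity to single events does not show the fault. That is correct. The fault is that the comparison has no free control count. Nor is the result a foregone conclusion: at assumed rates of 1% to 3% it could go either way.

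**Conclusion.** The point holds as a mismatch between a stated outcome and its stated test. On the plain wording, the P-value for RIC-related events reflects only the RIC-arm count, crossing 0.05 at 4/200 uncorrected or 6/200 by Yates or Fisher. The item gives no valid between-arm comparison of local cuff-type harm.

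This rests on three assumptions: that related to RIC means attributed to RIC actually received, that no control receives RIC in error, and that the arms have about 200 patients each. If the authors mean leg or cuff events of any cause, the zero is not structural and the point becomes one of naming and definition. The thresholds are arithmetic; the chances in the table depend on assumed rates.

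The weight is modest. This is one secondary safety outcome, and the primary analysis, the sample size and the other safety comparisons are untouched. It should still be changed, because a P-value that compares nothing is easily quoted as evidence for or against harm.

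**What to change.** - Remove RIC-related events from the list of outcomes tested by chi-square. Report them descriptively in the RIC arm only, as the number and percentage of patients with an exact 95% confidence interval.
- Compare the arms on adverse events regardless of attribution: any event, serious events, and leg or cuff-site events and pain. Give each as a risk difference with a 95% confidence interval, from the data already scheduled in Table 2.
- If the authors mean leg or cuff events of any cause in both arms, rename the outcome and define it without reference to RIC. The two-arm comparison can then stay.
- In the same edit, reconcile the safety population. The Statistical analysis section limits it to patients who received at least one protocol treatment, while the Discussion uses everyone randomized. If protocol treatment means RIC, the former leaves no control arm for any safety comparison.

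The cost is a change of wording and one extra table, with no new data collection if Table 2 applies to both arms. One limit remains: dropping attribution does not remove differences in how readily events, and pain above all, are reported in an open-label trial. The report should say so.

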### Patient population

We will recruit patients diagnosed as having had an acute ischemic stroke *via* brain MRI and/or CT. All 14 Japanese stroke centers and their prehospital regional centers will be invited to participate. The inclusion and exclusion criteria are listed in Table 1, and the baseline assessments and study procedures are provided in Table 2 and Figure 1. Participants need to show a defined ischemic lesion on magnetic resonance imaging (MRI). Patients who received alteplase treatment or mechanical thrombectomy can be enrolled 12 h after the intervention. All patients will provide written informed consent in the acute phase. If the research participant is an adult who is objectively judged to lack the capacity to give informed consent due to a speech or writing impairment caused by a stroke, the consent may be obtained from the legal representative.

**Table 1 T1:** Inclusion and exclusion criteria.

**Inclusion criteria**	**Exclusion criteria**
• Patients hospitalized in participating institutions	• mRS >2 before stroke onset
• Male and female patients (age range, 20–90 years)	• Planned intravenous rt-PA and/or EVT after registration
• Diagnosed as acute ischemic stroke by performing brain MRI and/or CT	• Within 12 h after rt-PA administration or EVT
• Within 48 h after stroke onset	• Systolic blood pressure ≥180 mmHg
• NIHSS scores range from 5 to 20 at registration	• History of PAD
• Tolerance to systemic blood pressure measurement and systolic blood pressure <180 mmHg	• Pregnant patients or patients suspected of being pregnant
	• Patients deemed unsuitable as participants by the investigator

CT, computed tomography; EVT, endovascular treatment; MRI, magnetic resonance imaging; NIHSS, National Institutes of Health Stroke Scale; PAD, peripheral arterial disease; rt-PA, recombinant tissue-type plasminogen activator.

**Table 2 T2:** Study procedures for eligible patients with acute ischemic stroke.

**Procedures/Data collection**	**Screening (days 0–1)**	**Registration/ Baseline visit 1 (day 1)**	**Visit 2 (day 3)**	**Visit 3 (day 7)**	**Visit 4 (day 30 or discharge)**	**Visit 5 (day 90 ±14 days)**

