**Enrollment**						
Informed consent	×					
Demographic characteristics	×					
Confirmation of patient background and medical history	×					
Randomization	×					

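### The NIHSS change outcome has two definitions, is analysed without baseline adjustment, and carries a power of 0.80 that is not derived anywhere

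*Protocol article*

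**What the plan says.** Three sections of the protocol article bear on this secondary outcome.

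- **Secondary outcomes** lists it as "change in NIHSS scores from before RIC to after RIC".
- **Statistical analysis of secondary outcomes** describes it as "The change in NIHSS score from the time of enrollment to 1 week later", to be "evaluated in a two-sided analysis of variance, with α = 0.05 and power = 0.80". No covariate is named.
- **Sample size calculation** contains the only power calculation. It is for good functional outcome on the mRS, 35% in controls against 50% with RIC: "with 80% power at the 5% significant level, a sample size of 334 patients is necessary". It gives no NIHSS difference and no NIHSS standard deviation, and neither appears elsewhere in the article.

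The Intervention section sets RIC once daily "for a minimum of 3 days and a maximum of 7 days", whereas "the control group will only undergo blood pressure measurements before and after the intervention period", that period being the 40 minutes of one session. Table 2 schedules NIHSS at screening, Visit 1, day 3, day 7 and day 30 or discharge, and puts "Randomization" in the screening column. Eligibility requires that "NIHSS scores range from 5 to 20 at registration".

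**The concern.** Three things in the NIHSS text do not fit together.

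**Power.** Power depends on an assumed difference, a standard deviation and a sample size; it is not a setting of a test in the way that alpha is. Written beside the analysis of variance, 0.80 reads as an established property of this comparison. A reader of a null NIHSS result could then take it as coming from an analysis known to have 80% power.

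**Definition.** The end of RIC and one week are different time points for any patient treated for fewer than seven days. Controls have no RIC course, so a score after RIC has no counterpart in that arm unless a matching date is assigned. The Randomization section conceals allocation only from the physician who rates the 90-day mRS, so NIHSS raters may know the arm. A fixed, common date is worth more in that setting.

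**Model.** Baseline NIHSS is recorded in everyone and can range from 5 to 20. Comparing raw change scores without it may give away precision and leaves the comparison exposed to chance baseline imbalance.

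**Working it through.** **1. What the stated 80% belongs to.** Inputs from Sample size calculation: 0.35 and 0.50, two-sided 5%, power 80%. With the unpooled-variance formula:

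n per arm = (0.35 × 0.65 + 0.50 × 0.50) × (1.960 + 0.842)² / 0.15² = 0.4775 × 7.85 / 0.0225 ≈ 166.6, rounded up to 167, so N = 334.

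The published figure reproduces exactly. None of its inputs concerns the NIHSS.

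**2. What 80% would mean for the NIHSS.** The 400 planned patients less 10% leave 360, or 180 per arm. The detectable standardised difference is

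d = (1.960 + 0.842) × √(2/180) = 0.295 SD of the change.

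With 167 per arm it is 0.307, and with 200 per arm 0.280. In points, for assumed SDs of the change (the article gives none):

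| Assumed SD | Difference for 80% power | Power for 1 point | Power for 2 points |
|---|---|---|---|
| 4 | 1.18 | 0.66 | 0.997 |
| 6 | 1.77 | 0.35 | 0.885 |
| 8 | 2.36 | 0.22 | 0.66 |

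(180 per arm, two-sided 5%.) The figure of 0.80 lies inside the range that these assumptions produce, so the article's content neither confirms nor refutes it.

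**3. The two definitions.**

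| | Secondary outcomes | Analysis section |
|---|---|---|
| Start | before RIC | enrolment |
| End, RIC arm | after RIC, about day 3 to day 7 | one week |
| End, controls | none of their own | one week |

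The analysis-section version matches a scheduled assessment, Visit 3 on day 7. The starting score also needs naming: Table 2 has NIHSS at both screening and Visit 1, with randomisation in the screening column, so a Visit 1 score could be taken after allocation.

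**4. What baseline adjustment would gain.** Let s0 and s1 be the SDs of baseline and day-7 NIHSS and r their correlation.

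- Variance of the change: s0² + s1² − 2·r·s0·s1
- Residual variance under ANCOVA: s1²(1 − r²)
- Difference between them: (s0 − r·s1)², which is never negative

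If s0 = s1 (assumed), the ratio of ANCOVA to change-score variance is (1 − r²) / [2(1 − r)] = (1 + r)/2:

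| Assumed r | Variance ratio | A true power of 0.80 becomes |
|---|---|---|
| 0.5 | 0.75 | 0.90 |
| 0.7 | 0.85 | 0.86 |
| 0.8 | 0.90 | 0.84 |
| 0.9 | 0.95 | 0.82 |

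Entry limits baseline to 5–20, while day-7 scores are not limited, so s1 may exceed s0. With assumed s0 = 4, s1 = 5.5 and r = 0.75:

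- Change score: 16 + 30.25 − 33 = 13.25
- ANCOVA: 30.25 × (1 − 0.5625) ≈ 13.23

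The gain is then practically nil.

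**The case against.** The strongest reply is that little turns on any of this. The analysis section is the operative text; it fixes one time point for both arms, it matches the day-7 visit, and seven days is also the longest RIC course. The wording under Secondary outcomes can be read as shorthand for it. The power phrase alters no analysis, and the article openly sizes the trial on the mRS. ANOVA on change is unbiased under randomisation, already subtracts the baseline, and could gain a covariate in a fuller analysis plan.

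Much of this stands. The analysis as specified does have a common date in both arms, so it would be wrong to say that the planned comparison uses an end date existing in one arm only; that follows only from the other section's wording. The two sections still disagree in print, the power phrase still has no basis, and the article names a method without a baseline term.

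A reader might also infer that patients who die before day 7 are dropped, making this a comparison among survivors. The documents do not support that. No section says how early deaths are handled in this analysis, such handling is commonly left to the statistical analysis plan, and all-cause mortality is a secondary outcome with its own test.

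**Conclusion.** The point holds as a matter of clarity and efficiency for one secondary outcome. One outcome has two definitions, and the figure of 0.80 is underived. A reader might conclude that the NIHSS analysis lacks 80% power. That is not shown: it would have it for a true difference of about 0.295 SD of the change with 180 per arm, and the article gives nothing from which to judge whether such a difference is plausible.

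Nor is the ANOVA invalid or biased. In large samples ANCOVA is never less precise, and it guards against chance imbalance. The variance reduction of 25% to 5% for r from 0.5 to 0.9 rests on assumed equal variances and may be close to nil otherwise. All SDs and correlations used here are assumptions. The primary mRS conclusion is unaffected.

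**What to change.** - **Definition.** Align Secondary outcomes with the analysis section. In both, and for both arms, define the outcome as NIHSS at Visit 3 (day 7) against the pre-randomisation NIHSS, and name the assessment that supplies that baseline.
- **Model.** Analyse by ANCOVA with arm and baseline NIHSS. Further covariates such as severity class or age are optional.
- **Power.** Delete the 0.80, or replace it with the detectable difference: about 0.295 SD of the change for 180 per arm at two-sided 5% and 80% power, with any SD used to convert it to points stated as an assumption.

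The cost is wording in two sections. No new data are needed, because NIHSS is already scheduled at screening and day 7.
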